#### Secondary variables.

For each patient, the following data is obtained from the clinical history and through questionnaires:

*Demographic data:* Age in years,date of birth, sex, living situation, and educational level

1
*Clinical history data*
Prevalent diagnosisLoss of weight in the last yearGeriatric Depression Scale: The Geriatric Depression Scale (GDS) is a self-report measure of depression in older adults. Users respond in a “Yes/No” format. The GDS was originally developed as a 30-item instrument. Since this version proved both time-consuming and difficult for some patients to complete, a 15-item version was developed. The shortened form (GDS-S) is comprised of 15 items chosen from the Geriatric Depression Scale-Long Form (GDS-L). These 15 items were chosen because of their high correlation with depressive symptoms.Barthel Index: Barthel Index is an ordinal scale used to measure performance in basic activities of daily living, i.e., feeding, bathing, grooming, dressing, bowel control, bladder control, toileting, chair transfer, ambulation and stair climbing. The index also indicates the need for assistance in care. It is a widely used measure of functional disability. The index was developed for use in rehabilitation patients with stroke and other neuromuscular or musculoskeletal disorders, but may also be used for oncology patients.Lawton-Brody Instrumental Activities of Daily Living Scale: is an instrument to assess independent living skills. It takes approximately 10–15 minutes to administer and contains 8 items that are rated with a summary score from 0 (low functioning) to 8 (high functioning).Pfeiffer test: Also known as Short Portable Mental Status Questionnaire (SPMSQ), it is a brief test of 10 questions used to assess a person’s cognitive status, especially in older adults. It evaluates aspects such as memory, temporal and spatial orientation, and the ability to perform basic tasks.Predimed questionnaire: The adherence of participants to the Mediterranean diet will be assessed through the 14-item Mediterranean diet adherence screener (MEDAS) validated for the Spanish population in a phone interview with the participant [18]. It consists of two questions about eating habits, eight questions about the frequency consumption of typical foods of the Mediterranean diet, and four questions about the consumption of foods not recommended in this diet. Each question is scored with 0 (non-compliant) or 1 (compliant), and the total score (from 14 questions) ranged from 0 to 14, so a score of 14 points means maximum adherence [18].

*Anthropometric measurements* (in the case of the center has the facilities and densitometer):Total body dual-energy X-ray analysis using a DXA device for the measurement of bone mineral density (both overall and in regions of interest) and body composition (fat mass, muscle mass).

*Peripheral blood biochemical variables:* Leukocytes ml/mmc, Red blood cells ml/mmc, Hemoglobin g/dl, Hematocrit %, Red blood cell distribution width %, Platelets ml/mmc, Vitamin D ng/ml, TSH nmol/l, Glucose mg/dl, Glycated hemoglobin (diabetics only) %, Creatinine mg/dl, Sodium meq/dl, Potassium meq/dl, Calcium mg/dl, Phosphorus mg/dl, GPT u/l, GOT u/l, Phosphatase alkaline u/l, Total proteins g/dl, Albumin g/dl, Prealbumin mg/dl, Cholesterol mg/dl, Triglycerides mg/dl, HDL mg/dl, LDL mg/dl, and C-reactive protein mg/ml.

*Metabolomic analysis*

a)Exposome assay

A targeted quantitative metabolomics approach will be applied to analyze the plasma samples using liquid chromatography coupled with tandem mass spectrometry (LC-MS/MS), as described previously [19,20]. This method will employ analyte extraction and LC separation combined with selective mass-spectrometric detection using multiple reaction monitoring (MRM) pairs to identify and quantify metabolites.

The approach will allow for the comprehensive profiling of over 1100 metabolites, including dietary-derived metabolites (especially (poly)phenols and their microbiota-derived derivatives); other dietary markers such as non-(poly)phenolic compounds (e.g., glucosinolates, methylzanthines, alkaloids, amino acid derivatives such as peptides, S-allylcysteine, fatty acids, benzoxazinoids); environmental and lifestyle-related metabolites (such as pollutants, pharmaceuticals, nicotine and alcohol metabolites); and approximately 500 endogenous compounds involved in key metabolic pathways (e.g., amino acids and derivatives, lipids, vitamins, biogenic amines, organic acids, and carbohydrates). The panel will also include metabolites from the tryptophan-kynurenine pathway, as well as and microbial-derived metabolites such as indoles, bile acids, and short-chain fatty acids and others.

Plasma samples will be stored at −80 °C until analysis. For extraction, 10 μL of internal standard solution will be added to 100 μL of plasma, followed by 500 μL of cold acetonitrile (−20 °C) containing 1.5 M formic acid and 10 mM ammonium formate in the plate. After vortexing and incubation at −20 °C to induce protein precipitation, the extracts will be collected using a Waters Positive Pressure-96 processor (Waters, Milford, MA, USA), dried under a stream of nitrogen gas, and reconstituted in 100 μL of water:acetonitrile (80:20, v/v) containing 0.1% formic acid (v/v) and external standards. The samples will then be vortexed and prepared for injection.

Mass spectrometric analysis will be performed on a Sciex 7500 QTrap® instrument coupled with an Agilent 1290 UHPLC system. A Luna Omega Polar C18 column will be used for chromatographic separation, with distinct different gradients applied for positive and negative ion modes. The instrument will operate in scheduled MRM (sMRM) mode to ensure high sensitivity and selectivity for all targeted metabolites.

b)Clinical biomarkers assay

Plasma samples will be prepared and analyzed using a combination of direct flow injection tandem mass spectrometry (DFI-MS/MS) and liquid chromatography tandem mass spectrometry (LC-MS/MS) (20).

This targeted clinical biomarker assay will aim to provide a robust and user-friendly platform for the discovery and quantification of metabolomic biomarkers. The method will allow the targeted identification and quantification of up to 651 metabolites from 18 different analyte groups, including amino acids and derivatives, biogenic amines, organic acids, nucleotide/nucleosides, lipids, acylcarnitines, and glycerophospholipids. The analytical workflow will combine analyte derivatization, extraction and high-throughput quantification using MRM in tandem mass spectrometry. For accurate quantification, the method will incorporate stable isotope-labelled internal standards, along with other compound-specific internal standards, across all metabolite groups.

*Healthcare resource use:* Number of Primary Care consultations, prescribed drugs (polypharmacy), contacts with the Secondary Care facilities during the study period.

Non-elective hospital admissions and number of admissions and length of stay during the study period.

*All-cause mortality.*

### Statistical analysis plan

Descriptive statistics will be used to summarize baseline characteristics of the study population. Continuous variables will be reported as means and standard deviations or medians and interquartile ranges, as appropriate, while categorical variables will be summarized using frequencies and percentages. All statistical analyses will be conducted using R software, and a two-sided significance level of 0.05 will be applied unless otherwise specified.

To identification of frailty phenotypes, unsupervised cluster partitioning methods will be applied to identify groups of individuals with similar patterns of deficits and clinical characteristics, thereby defining distinct frailty phenotypes. Specifically, k-means clustering and hierarchical clustering approaches will be used. Prior to clustering, variables will be standardized as appropriate to ensure comparability across measures. The optimal number of clusters and the quality of the clustering solutions will be evaluated using predefined validation criteria, including the gap statistic and silhouette index. These metrics will be used to assess cluster separation, cohesion, and stability, as well as the robustness of individual cluster assignments.

In a second step, a longitudinal follow-up will be conducted to record the onset and accumulation of health deficits throughout the study period, continuing until the end of follow‑up, death, or loss to follow‑up. To delineate distinct patterns of frailty progression over time, we will apply latent class analysis using mixed growth models or comparable latent trajectory modelling approaches. These methods will allow to identify differential longitudinal trajectories characterized either by varying rates of deficit accumulation (capturing acceleration in frailty development) or by distinct combinations of specific deficits or phenotypic characteristics.The resulting models will classify participants into latent clusters representing heterogeneous frailty trajectories, enabling the identification of subgroups at higher risk of accelerated decline and facilitating targeted intervention strategies.

Finally, the identified frailty phenotypes and patient clusters will be examined in relation to clinically relevant health outcomes, including the utilization of health care services in both primary and secondary care settings, hospital admissions, biomarker profiles, and mortality. Appropriate regression models will be used depending on the outcome of interest, and results will be reported using effect estimates with corresponding 95% confidence intervals. Where applicable, analyses will account for follow-up time and relevant covariates. These analyses will enable the assessment of the prognostic and clinical relevance of the identified frailty phenotypes and trajectories.

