## Abstract

Frailty has become a major challenge for health systems, but it also presents a window of opportunity to fight disability through preventive strategies focused on the detection and treatment of frailty across all care settings. However, no systematic strategies for screening and early detection are currently available in clinical practice. This project aims to identify clinical and biological phenotypic clusters that drive progression through the different stages of frailty, and to describe the underlying mechanisms of the trajectories leading to disability and potential treatment interventions. In addition, the Frailty Trait Scale 5 (FTS5) will be validated as a practical tool for implementation in both primary care and hospital settings. A prospective, population-based cohort (CohorFES) will be established for frailty phenotyping. A CIBERFES Biobank will also be created to store blood and urine samples from CohorFES participants for future research. Demographic and clinical history data, anthropometric measurements, the PREDIMED questionnaire, peripheral blood biochemical variables, and metabolomics data will be collected at baseline and annually until participants develop frailty. Cluster partition models (k-means and hierarchical clustering) will be used to group individuals with similar deficits and characteristics (frailty phenotypes). Then, by using pre-established criteria (gap and silhouette), the proposed clustering solution (belonging to given clusters) will be evaluated. We will also assess, in a longitudinal manner, the emergence and accumulation of deficits over time, identifying subgroups with more rapid progression. The results will be used to define and compare clusters and progression trajectories. Finally, frailty phenotypes and patient clusters will be correlated with health outcomes such as healthcare utilization (primary and secondary care), hospital admissions, and mortality. Information on clinical and biological phenotypic clusters involved in the progression of frailty may help identify potential therapeutic targets to improve the management of these patients. In summary, from a research perspective, this project aims to improve our understanding of the interindividual variability in clinical trajectories that lead to frailty, dependence, and ultimately, death.

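### The plan assigns the assessment of cluster stability to the gap statistic and silhouette index, which do not measure recurrence, so phenotypes that do not replicate could be reported as stable

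*Protocol article*

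**What the plan says.** The Statistical analysis plan section of the protocol article fixes the methods: "Specifically, k-means clustering and hierarchical clustering approaches will be used". The number of clusters and the quality of the solutions are to be "evaluated using predefined validation criteria, including the gap statistic and silhouette index". The next sentence gives those criteria four tasks: "These metrics will be used to assess cluster separation, cohesion, and stability, as well as the robustness of individual cluster assignments".

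The Abstract names the same two criteria and no others: "by using pre-established criteria (gap and silhouette), the proposed clustering solution (belonging to given clusters) will be evaluated".

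The article describes no bootstrap, split-sample, between-centre or external replication step. It plans two clustering methods but does not present agreement between them as a check. The clusters are then carried forward: "Finally, the identified frailty phenotypes and patient clusters will be examined in relation to clinically relevant health outcomes".

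**The concern.** Of the four properties in that sentence, separation and cohesion are what the two indices were built for. Stability is a different property. It asks whether the same groups would return if other people had been sampled, or if one centre were left out. An index computed once, on one fitted partition, holds no information of that kind.

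The clinical and biological phenotypes are part of the stated main goal, and their links with health care use, admissions, biomarkers and mortality are to show their prognostic relevance. The Discussion also wants them to support early detection and to supply homogeneous groups for later research. Those uses assume that the groups recur. Six centres are listed under Study design and setting, and the Limitations section calls data homogeneity a key factor. A cluster that reflects one centre's case mix or measurement practice can be compact and well separated in the pooled data and still be absent elsewhere. As written, good gap and silhouette values could be reported as evidence against this.

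**Working it through.** The plan gives no figure to reproduce. The check is by definition first and by illustration second.

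**Definitions**

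- Silhouette for person i: s(i) = (b − a) / max(a, b). Here a is the mean distance to the others in the same cluster, and b is the smallest mean distance to the members of another cluster. It needs at least two clusters.
- Gap for k clusters: Gap(k) = E*[log W_k] − log W_k, where W_k is the within-cluster dispersion and E* is taken over data simulated from a reference distribution without clusters. It can be evaluated at k = 1.
- Clusterwise stability: refit on resample X*, match each cluster C to its best counterpart C*, and average |C ∩ C*| / |C ∪ C*| (Jaccard) over resamples.

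The first two are functions of one data set and one partition. The gap statistic does involve simulation, but its draws come from the reference distribution and not from the cohort. Its standard error is therefore Monte Carlo error in the reference, not sampling variation in the clusters. Only the third quantity refits on resampled data. This settles the point without any simulation.

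**Illustration**

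Assumptions, none from the documents: n = 500; 10 standardised variables (2 for the disc); k-means only; k up to 6; gap with a box-shaped and a PCA-aligned uniform reference (20 draws each); 50 bootstrap refits; one seed. The one-factor data have pairwise correlation 0.5. The skewed data have one exponential factor carrying 0.7 of the variance.

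| Structure | Gap k (box / PCA) | Best silhouette | Jaccard at that k | Silhouette at k = 4 | Jaccard at k = 4 |
|---|---|---|---|---|---|
| One-factor continuum | 3 / 1 | 0.25 (k = 2) | 0.95, 0.95 | 0.12 | 0.73–0.81 |
| Skewed continuum | 5 / 1 | 0.44 (k = 2) | 0.96, 0.88 | 0.19 | 0.54–0.88 |
| Independent Gaussian | 1 / 1 | 0.08 (k = 2) | 0.56, 0.53 | 0.07 | 0.33–0.48 |
| Uniform disc | 1 / 1 | 0.40 (k = 4) | 0.84–0.89 | 0.40 | 0.83–0.88 (second bootstrap run) |
| Three true clusters | 6 / 3 | 0.42 (k = 3) | 1.00 each | 0.32 | 0.76–1.00 |

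Four readings follow.

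1. Silhouette does not rank stability. At k = 4 the skewed data have the higher silhouette (0.19 against 0.12) but the less stable worst cluster (0.54 against 0.73).
2. The gap statistic is a partial safeguard. It chose k = 1 in the independent Gaussian and disc data with both references. In the two continua it chose k = 1 with the PCA reference, but 3 and 5 with the box reference.
3. Stability is not proof of clusters. The two continua have no clusters, yet give Jaccard 0.88–0.96 at k = 2.
4. Silhouette carries some information on individual assignment. In the Gaussian and one-factor data (k = 2 and 3), its Spearman correlation with the bootstrap reassignment rate was −0.57 to −0.71.

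**Larger samples**

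Two further runs used n = 1,290 (215 + 1,075 from the Sample size section), 15 correlated variables, no true clusters, the PCA reference and 15 refits, with six data sets per run. Silhouette peaked at k = 2 and gap chose k = 1 in all 6 + 6 = 12. At k = 4, one-factor data gave silhouettes of 0.075–0.091 with Jaccard 0.82–0.91. Three-factor data gave slightly higher silhouettes, 0.092–0.099, with Jaccard 0.44–0.68 in five of six data sets and 0.84–0.86 in the sixth.

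**The case against.** The strongest reply is that this is one word in a condensed article. The criteria list is introduced as open, two clustering methods are planned, and resampling detail belongs in a full analysis plan that is not shown. It is true that the absence of a bootstrap specification would not be a finding by itself. But the article does not leave stability for later. It assigns stability to metrics, and the only ones it names, there and in the Abstract, are gap and silhouette.

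A reader might go further than the documents allow in three ways.

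- *That neither index bears on individual assignments.* Silhouette width is calculated per person and tracked bootstrap reassignment in simulation. It is a recognised, though indirect, measure of how clear an assignment is.
- *That irreproducible phenotypes would pass validation.* No acceptance threshold is stated, and the indices do flag some bad solutions, as in the Gaussian case. In the larger simulations gap chose one cluster every time.
- *That the clusters feed every later analysis.* The progression trajectories come from a separate latent class or growth model step, and the FTS5 validation compares three frailty instruments. Only the association analyses use the clusters.

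The simulations also have fair critics. The documents fix none of the structures, variable counts or numbers of refits. In the large samples k = 4 was set for comparison and selected by neither criterion. The plan would compare solutions within one data set, not silhouettes across data sets. All of this limits what the figures show; the definitional point does not depend on them.

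**Conclusion.** The point holds for stability. The plan gives two internal, single-sample indices a property that they do not have, so phenotypes that fail to recur across resamples or centres could be described as stable. It does not hold for assignment robustness in the looser sense of assignment clarity, and it does not show that false phenotypes would be accepted.

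Its size in this cohort is unknown, because no cluster data or list of clustering variables is given. The simulated figures show only that silhouette and stability can part company. What is at stake is whether the phenotypes may be called stable and how much weight their associations with outcomes can bear. The trajectory models and the FTS5 validation are not affected. The sentence should be corrected before the clustering is run; the Gantt chart dates data analysis from January 2028.

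**What to change.** Limit the gap statistic, evaluated from k = 1, and the silhouette index to the number of clusters, separation, cohesion and clarity of individual assignment. Then do one of two things.

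- **Keep the stability claim and support it.** Add bootstrap refits (for example 100) with clusterwise Jaccard, which R's clusterboot provides. Add the adjusted Rand index between the k-means and hierarchical solutions, as a check on dependence on the method, and a leave-one-centre-out refit over the six centres.
- **Or delete the word** and make no statement about stability.

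Any Jaccard cut-off should be prespecified by the sponsor and read together with gap. Taken alone, a cut-off such as 0.75 would accept the two-cluster splits of both continua above (0.88–0.96), which contain no clusters. If gap selects k = 1, the report should say that discrete phenotypes were not supported.

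Possible wording: *The gap statistic (from one cluster upwards) and silhouette index will inform the number of clusters, their separation and cohesion, and the clarity of individual assignments; stability will be assessed by bootstrap refitting, agreement between the two clustering methods and leave-one-centre-out refitting.*

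The cost is a few lines of R and a sentence in the plan, with no new data. The downside is that fewer clusters may be reportable as stable phenotypes.

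### Latent trajectory classes built from the whole follow-up are related to mortality, admissions and care use in that same follow-up, so the associations cannot be read as prognostic

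*Protocol article*

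**What the plan says.** The Statistical analysis plan section of the Protocol article has three steps.

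- **Phenotypes.** K-means and hierarchical clustering group people with similar deficits.
- **Trajectories.** A longitudinal follow-up is conducted "to record the onset and accumulation of health deficits throughout the study period", ending at end of follow-up, death or loss to follow-up. Growth mixture or comparable latent trajectory models are fitted, and "The resulting models will classify participants into latent clusters representing heterogeneous frailty trajectories".
- **Outcomes.** Then "the identified frailty phenotypes and patient clusters will be examined in relation to clinically relevant health outcomes", among them care use, admissions and mortality. The section concludes: "These analyses will enable the assessment of the prognostic and clinical relevance of the identified frailty phenotypes and trajectories".

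The outcome window is given under Secondary variables: "Non-elective hospital admissions and number of admissions and length of stay during the study period". Contacts with care are counted over the study period too, and all-cause mortality is listed without a separate window.

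The only stated safeguard is: "Where applicable, analyses will account for follow-up time and relevant covariates".

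**The concern.** The class is an exposure that is known only after the follow-up in which the outcome occurs. To be recognised as a fast progressor, a person must live through enough annual visits for the slope to show. Someone who dies early leaves one or two measurements and is placed in whichever class is larger. The exposure is therefore partly a record of survival, and it is then used to explain survival.

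A survival model or an offset starting at the baseline visit (V0) takes the class as given at V0. It corrects for how long each person was at risk, but not for the fact that time at risk helped to decide the class.

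For admissions and care use there is a different problem: an admission can worsen the deficits that later define the class.

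At stake is the last analysis step, which is meant to show that the trajectories matter clinically. Its mortality result could be wrong in size and in sign.

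**Working it through.** The article gives no figure for this analysis. Its sample size (215 and 1,075) concerns incident frailty and is not used here.

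**Inputs from the document.** 1,500 participants; recruitment from January 2021 to December 2027; annual visits (Study schedule). Follow-up is listed to 31 December 2029 (Gantt chart). Follow-up therefore lasts about 2 to 9 years per person.

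**Assumed inputs, since the document gives none.** Two classes with the same mean at V0; slopes 0.5 and 2.5 points per year; between-person SD σu = 4; residual SD σe = 3; fast-class share π = 0.25; death hazard 5% per year, unrelated to class.

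**Step 1: how class assignment depends on the number of visits.** Take the best case, in which the model parameters are known exactly. With k visits, the class means differ by d_j = 2j, j = 0,…,k−1. Then

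D² = (1/σe²) [Σd_j² − σu²/(σe² + kσu²) × (Σd_j)²], L = ln((1−π)/π) = ln 3 = 1.099,

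P(assigned fast | fast) = Φ(D/2 − L/D), P(assigned fast | slow) = Φ(−D/2 − L/D).

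| Visits | D² | Fast people called fast | Slow people called fast | All called fast |
|---|---|---|---|---|
| 1 | 0 | 0 | 0 | 0 |
| 2 | (4 − 16/41 × 4)/9 = 0.271 | 0.032 | 0.009 | 0.015 |
| 3 | (20 − 16/57 × 36)/9 = 1.099 | 0.300 | 0.058 | 0.119 |
| 5 | (120 − 16/89 × 400)/9 = 5.343 | 0.752 | 0.051 | 0.227 |

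The last column is 0.25 × (fast) + 0.75 × (slow); for three visits, 0.25 × 0.300 + 0.75 × 0.058 = 0.119. The true share is 0.25 in every row. Nobody who dies before the first annual visit can be called fast. With π = 0.60 the pull reverses: with one visit everyone is called fast, and with three visits 0.669 are.

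**Step 2: effect on mortality.** Simulation with 300 runs per setting: 1,500 people, uniform entry over 7 years, end at year 9, Cox model from V0.

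| Setting | Truth | Whole-follow-up class: median HR (p<0.05) | V2 landmark: median HR (p<0.05) |
|---|---|---|---|
| Hazard 2%, 5%, 8% | 1.0 | 0.47, 0.47, 0.46 (93%, 100%, 100%) | 0.98, 1.01, 0.99 (4%, 6%, 4%) |
| Well-separated classes (slope 4, σe = 2) | 1.0 | 0.66 (83%) | 0.99 (6%) |
| Fast class 60% | 1.0 | 1.76 (100%) | 0.98 (4%) |
| Visits stop at frailty | 1.0 | 0.48 (99%) | 1.00 (2%) |
| Real effect | 2.0 | 0.72 (70%) | 1.35 (39%) |

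The landmark takes class from the baseline, one-year and two-year visits (V0 to V2) and counts deaths after V2. With the true class in place of the assigned one, the null hazard ratio is 0.99 to 1.01. A separate simulation with hazards of 3 to 8% per year gave null rate ratios of 0.40 to 0.41 (25% fast) and 1.85 to 1.94 (60% fast). It showed a true ratio of 2 as 0.56 to 0.60, and its landmark stayed at 0.97 to 1.02 under the null.

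**Step 3: admissions.** Assume 0.2 admissions per year and no class effect. Raw counts give a ratio of 1.20 (80% rejection); with a person-time offset it is 1.00 (4%). If each admission adds 2 points to later scores, the offset analysis gives 1.53 (100%) and the V2 landmark gives 1.00 (5%).

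**Step 4: deaths lost to a V2 landmark.** At hazard 0.05, the chance of death by year 2 is 1 − e^(−0.10) = 0.095. The chance of an observed death, with follow-up uniform on 2 to 9 years, is 1 − (e^(−0.10) − e^(−0.45))/(0.05 × 7) = 0.237. The share lost is 0.095/0.237 = 40%. At hazards of 3% and 8% it is 39% and 43%.

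**The case against.** The strongest reply is that this is a condensed article. It promises only suitable regression models, gives no time origin, and leaves the trajectory model family open, so a full analysis plan could use a joint model or a landmark. That is fair as far as it goes. A reader might infer that the plan fixes a Cox model from V0, or treats dropout through death as ignorable; neither is stated. What stands is that the article itself sets the two overlapping windows and the prognostic reading. The one remedy it names, follow-up time, does not repair the mortality analysis. A later document would have to change what is written, not merely add detail.

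Four further objections hold and limit the point.

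- The words about phenotypes and clusters also cover k-means and hierarchical groups. If these are formed on V0 data, they are known at the time origin and are not affected.
- A reader might extend immortal time to admissions. Step 3 shows that an offset removes that part; only reverse causation is left.
- The Study schedule says that each participant completes at least three visits. Restricting to such people shrinks the mortality bias but does not reliably remove it (HR 0.75 to 1.10 under the null, rejection 6 to 42%).
- The V2 landmark is not a near-free remedy, as Step 4 and the last row of Step 2 show.

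**Conclusion.** The plan is wrong as written for the latent trajectory classes, and only for them. For mortality, class membership depends on survival, and accounting for follow-up time does not cure this. A true null can appear as a ratio of about 0.4 to 0.7 when the fast class is a minority, and about 1.8 to 1.9 when it is the majority. A real doubling of risk can appear as a reduction.

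A reader might infer that fast progression will always look protective, or that one of these ratios is a forecast. Neither follows. Size and direction depend on class share and separation, and the death hazard, slopes, variances and class shares are all assumed. The figures show that the bias can be large, not how large it will be here.

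For admissions and care use, the remaining problem is reverse causation. Its size (1.53 in the illustration) depends entirely on how strongly admissions are assumed to worsen later scores.

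The aims of finding clusters and validating the FTS5 are not touched. The change should be made before the trajectory-outcome results are presented as prognostic; the Gantt chart lists data analysis as pending, with a start in January 2028.

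**What to change.** - **Mortality, primary:** fit a joint latent-class model of the deficit trajectory and time to death. It keeps all deaths and carries the uncertainty of class membership. Since its classes are informed by survival as well as deficits, report individual prognosis as predicted risk given the deficits seen up to a stated visit.
- **Mortality, sensitivity:** use a landmark at V2, with classes from V0 to V2 data only and deaths counted after V2 among those alive and under follow-up.
- **Admissions and care use:** use the same V2 landmark, with a person-time offset.
- **Otherwise:** describe associations between whole-follow-up classes and outcomes as descriptive, and drop the prognostic claim for trajectories.
- **Baseline phenotypes:** state that they are formed on V0 data; V0 then remains their time origin.

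**Cost.** No visit, sample or data item changes. The joint model needs more analysis work and rests on its own assumptions about how trajectory and death are linked. The landmark loses roughly 40% of deaths under uniform entry. With 500 recruited so far, it loses 50 to 57% if the other 1,000 are assumed to enter in 2026 and 2027. It also attenuates real effects, because slopes from three visits are noisy: a true ratio of 2 appeared as about 1.2 to 1.35.
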